## Abstract

**Background:**

In India, heavy menstrual bleeding or menorrhagia (*Raktapradara*) constitutes about 15% to 20% of all gynecological admissions in an institution. Of these, 43% of patients are aged 20-40 years. This condition is worsening because of the high prevalence of anemia among Indian women. Menorrhagia can have a significant impact on women’s lives. Medical treatment is usually the first choice in excessive bleeding, but it reduces menstrual blood loss by only 50%, and up to 50% of women undergo surgical treatment within 5 years. However, none of these treatments proved their definite efficacy in spite of the high price and side effects. This condition presents a major financial burden on health care services. In Ayurveda, encouraging work has been done on the compound drug *Ashokarishta*, and the drug *Trinakantamani pishti* is indicated in Ayurvedic classics and the *Ayurvedic Formulary of India*. Also, these medicines have been used in Ayurvedic practice for a long time. However, no clinical trial has been carried out on these formulations.

**Objective:**

The primary objective is to evaluate the efficacy of Ayurvedic intervention in the management of menorrhagia, and the secondary objective is to assess the efficacy of Ayurvedic intervention on the quality of life of the women with menorrhagia.

**Methods:**

This ongoing study is an open-label, interventional, randomized controlled trial, with a sample size of 140 in the treatment and control groups combined (including 20% dropouts), and will be carried out within the duration of 36 months. Participants in the treatment group will receive Ayurvedic treatment, that is, 20 mL of *Ashokarishta*, 250 mg of *Trinakantamani pishti*, and 1 iron and folic acid tablet (100 mg of elemental iron and 1.5 mg of folic acid) twice a day orally for 3 months. Participants in the control group will receive a 500-mg tranexamic acid tablet thrice a day for 7 days from the first day of menses for 3 cycles and 1 iron and folic acid tablet twice a day orally for 3 months. The primary outcomes are changes in the amount of uterine bleeding evaluated by the Pictorial Blood Loss Assessment Chart, changes in the duration of bleeding, and attainment of a normal quantity of blood loss during the interval of cycles. The secondary outcome is changes in the Menorrhagia Impact Questionnaire.

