### Sample Size

To calculate the sample size, we anticipated a difference of 70 units in average PBAC score after treatment between the two groups (*Trinakantamani*
*pishti* along with *Ashokarishta* vs tranexamic acid tablet), with an SD of 137 units based on the results of the previous study [14]. With 95% confidence level (α=.05) and 80% power, the number of patients to be enrolled in the study was calculated using the following formula:

where *Z*_1 – α/2_=1.96, *Z*_1 – β_=0.84, σ=137, and δ=70.

Expecting a dropout rate of 15%, the number of patients is estimated to be 60 + 9 = 69. Thus, approximately 70 patients should be enrolled in each group.

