### Randomization and Allocation

A randomization chart will be generated with the help of computer-generated random numbers. Participants will be randomized in a ratio of 1:1 to either of the two groups. The randomization schedule will be strictly controlled and remain with the biostatistician/data analyst. Sequentially numbered, sealed, opaque envelopes will be used to conceal the allocation.

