### Statistical Methods

Continuous variables will be presented as mean, SDs, medians, and ranges. Categorical variables will be summarized with frequencies and percentages. When inferential analyses will be conducted for continuous variables, they will be tested for normality. Nonparametric methods will be used to compare nonnormal data. Within-group comparison will be done using a paired *t* test (1- or 2-tailed, as suitable), while between-group comparisons will be done using an independent sample *t* test (1- or 2-tailed, as suitable) for the data following normal distribution. Nonnormal data within the group will be compared using the Wilcoxon sign rank test, while between groups comparison will be done by using the Mann-Whitney *U* test. Categorical data between groups will be compared using the chi-square or Fisher exact test. A 2-sided *P* value of <.05 will be considered statistically significant. Per-protocol and intention-to-treat analyses will be carried out at the end of the study. All data will be analyzed using Stata (version 16.1; Stata Corp).

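### The abstract says the 140 participants include a 20% dropout allowance, but the Sample Size section derives the same 140 from 15%, and 140 holds only about 14 to 15%

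*Protocol article*

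**What the plan says.** The Methods paragraph of the Abstract describes the trial "with a sample size of 140 in the treatment and control groups combined (including 20% dropouts". It gives no power figure.

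The Sample Size section plans on a normal-theory comparison of two means. The anticipated effect is given as "we anticipated a difference of 70 units in average PBAC score after treatment between the two groups", "with an SD of 137 units based on the results of the previous study", and the error rates as "With 95% confidence level (α=.05) and 80% power". The allowance for loss follows: "Expecting a dropout rate of 15%, the number of patients is estimated to be 60 + 9 = 69". The section then concludes: "Thus, approximately 70 patients should be enrolled in each group". Two groups of 70 make the Abstract's 140.

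Allocation is equal (Randomization and Allocation: "Participants will be randomized in a ratio of 1:1 to either of the two groups"), and the test is two-sided at 5% (Statistical Methods: "A 2-sided *P* value of <.05 will be considered statistically significant").

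**The concern.** The same total is said to absorb 20% dropout in one place and is derived from 15% in another. Both statements are current text, and the article does not say which rate the sponsor holds to.

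The rate decides what the trial can be said to deliver. A reader of the Abstract alone will believe that one participant in five can be lost within the planned numbers. If the calculation was built for a smaller loss, that allowance does not exist, and power at 20% loss falls below the 80% used in planning.

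The section also adds 15% of the evaluable number instead of dividing by the proportion expected to remain, so it is worth checking whether that matters as well.

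**Working it through.** **Inputs.** Difference δ = 70, SD σ = 137, Z = 1.96 and 0.84, dropout 15%, about 70 per group (Sample Size). Dropout 20%, total 140 (Abstract). Allocation 1:1 (Randomization and Allocation). Two-sided 5% (Statistical Methods).

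**Step 1: reproduce the plan's figure.**
n per group = 2 × (1.96 + 0.84)² × σ² / δ² = 2 × 7.84 × 18,769 / 4,900 = 60.06.
The stated 60 is reproduced (61 if rounded up). The stated 69 is also reproduced: 60 × 1.15 = 69.

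**Step 2: what allowance does 70 per group hold?**
Going from 70 to 60 is a loss of 10/70 = 14.3% of those enrolled.

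| Dropout | Added: 60 × (1 + d) | Divided: 60 / (1 − d) | Divided, starting from 61 |
|---|---|---|---|
| 15% | 69 | 70.6, so 71 | 71.8, so 72 |
| 20% | 72 | 75 | 76.3, so 77 |

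At 15%, either method lands close to 70. At 20%, neither does: the totals would be 144 by adding, or 150 to 154 by dividing.

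**Step 3: power after loss, counting completers only.**
Power ≈ Φ(δ / (σ√(2/n)) − 1.96), with δ/σ = 70/137 = 0.511.

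- 15% loss: n = 70 × 0.85 = 59.5. Φ(0.511 × √29.75 − 1.96) = Φ(0.827) = 79.6%. By the noncentral t, 78.9%.
- 20% loss: n = 70 × 0.80 = 56. Φ(0.511 × √28 − 1.96) = Φ(0.744) = 77.1%. By the noncentral t, 76.4%.

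**Step 4: difference detectable at 80% power with 56 per group.**
(1.96 + 0.84) × 137 × √(2/56) = 383.6 × 0.1890 = 72.5 units, against the planned 70.

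**Step 5: size of the add-versus-divide error.**
Dividing by 0.85 gives 71 per group where the section has 69. Rounding 69 up to 70 leaves a gap of one participant per group, and power at 15% loss stays at about 79 to 80%.

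**The case against.** The strongest reply is that this is a stray figure in an abstract. The Sample Size section holds the only derivation, 140 follows from its 15%, and at that rate the design delivers what it claims. That is the simplest reading and may well be right. It does not remove the inconsistency, because the article does not say which rate is intended.

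A reader might go further and infer that the protocol claims 80% power at 20% dropout and is therefore underpowered. The document does not support this. The Abstract attaches no power to its 20%, and the 80% appears only in the Sample Size section, beside 15%. The 76 to 77% is conditional on 20% being the true expectation.

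It is also a complete-case figure. The article plans an intention-to-treat analysis, mentions imputation for dropouts, and schedules repeated PBAC assessments, so some who leave may contribute data. Imputation does not necessarily restore the lost information, so this softens the figure without cancelling it.

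A reader might likewise treat the added 15% as a material fault in the sample size. It is a mistake of method, but rounding to 70 absorbs nearly all of it.

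Finally, a loss of about 3 to 4 points of power and a shift of 2.5 units against an SD of 137 are small. That stands, and it limits the weight of the point.

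**Conclusion.** The point holds as an inconsistency with a modest, quantified consequence. The two dropout rates contradict each other, and the Abstract's 20% cannot be obtained from the protocol's own inputs: 140 carries an allowance of about 14 to 15%.

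At 15% loss the planned power is essentially met (79.6% by the normal formula, 78.9% by the t test). At 20% loss it is 77.1% or 76.4%, with about 72.5 units detectable at 80% power. These figures rest on the stated difference and SD, equal loss in the two groups, a two-sided 5% test, and no data from dropouts.

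Nothing here shows that the design fails at the rate on which it was calculated.

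**What to change.** Keep 140, have the sponsor confirm which rate was intended, and state that one rate in both the Abstract and the Sample Size section.

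- **If 15%:** change the Abstract to 15% and state that 70 per group gives about 79 to 80% power after that loss.
- **If 20%:** change the Sample Size section to 20%, replace the 60 + 9 step, and restate the power with 140 enrolled as about 76 to 77% in place of 80%, or give the detectable difference at 80% power as about 72.5 units.

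In either case, show the allowance as evaluable number divided by (1 − dropout), say that 70 was fixed by rounding, and label the power as complete-case. Division does not return exactly 70 at either rate, so the text should report what 70 delivers and not present it as the result of the division.

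The cost is a few restated figures. No participants are added, and no endpoint, analysis or trial procedure changes. The article reports 79 enrolled as of December 2024, with analysis to be completed by February 2026; the correction belongs before the analysis.

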**Results:**

As of December 2024, a total of 79 patients have been enrolled. Data analysis should be completed by February 2026. The study will be reported following standard guidelines for reporting randomized controlled trials. Clinical results will be disseminated through conferences and peer-reviewed publications in a relevant journal.

**Conclusions:**

The Ayurvedic approach may provide an evidence-based therapeutic tactic for the management of menorrhagia.

**Trial Registration:**

Clinical Trial Registry India CTRI/2023/05/052929; https://tinyurl.com/3cd6mxrn

**International Registered Report Identifier (IRRID):**

DERR1-10.2196/60801

## Introduction

Normal menstrual bleeding is cyclical, with 3-5 days in durations and 50-60 mL of bleeding in normal color, as described in Ayurvedic classics. However, when the normal menstrual bleeding pattern is altered in reference to duration, amount, color, and cycle, the conditions are called *Artavadushti*; *Raktapradara* is one of them, and it is comparable to menorrhagia. In India, menorrhagia constitutes about 15% to 20% of all gynecological admissions in an institution. Of these, 43% of patients are aged 20-50 years. This condition is worsening because of the high prevalence of anemia among Indian women [1]. Heavy menstrual bleeding (HMB) can have a significant impact on women’s lives. HMB or menorrhagia is clinically deﬁned as greater than or equal to 80 mL blood loss per menstrual cycle [2,3]. It is, however, the woman’s perception of her own menstrual loss that is the key determinant in a referral and, indeed, subsequent treatment. In allopathic medicine, various medical treatment options are available, but many women proceed to surgery due to treatment failure or hormonal side effects. Surgery introduces the risk of bowel, bladder, and ureteric damage, as well as hemorrhage, infection, and even death [4]. So, there is a clear unmet clinical need for better medical treatments for this benign but incapacitating condition. *Ashokarishta* is a compound drug, consisting of 14 drugs described in the *Stree rogadhikara* (female disorders) section of the *Bhaishajya Ratnavali* book of Ayurveda [5]. The *phalashruti* (benefits at the end of the composition) of this medicine says that, by using the medicine for more than one month, it cures pain due to menorrhagia, fever, several types of hemorrhages, hemorrhoids, etc. *Trinakantamani pishti* [6,7] is a drug also mentioned for *Raktapradara* (HMB or menorrhagia) in Ayurvedic classics. As the effect of this medicine is mainly in bleeding disorders, it was decided to evaluate its efficacy in *Raktapradara* (Table 1). Some encouraging work has been done on the effect of *Ashokarishta* [8-10] on *Raktapradara*, but no work has been carried out on *Trinakantamani pishti* along with *Ashokarishta*. Tranexamic acid is a safe and effective form of medical therapy in women with menorrhagia; it also increases the quality of life in these women [11]. So, this study is planned to evaluate the efficacy of Ayurvedic treatment modalities in the management of menorrhagia and to assess the efficacy of Ayurvedic intervention on the quality of life of the women with menorrhagia, compared to the control intervention (tranexamic acid).

**Table 1 table1:** Details of the investigational products.

Drug and components		Botanical name	Part used	Quantity
* **Trinakantamani pishti** *				
	1. Trinakantamani	—^a^	—	1 part
	2. Distilled rose water	—	—	As needed for *mardana* (triturate)
**Ashokarishta**				
	1. Ashok	*Saraca asoca* L.	Stem bark	100 parts
	2. Water for decoction (*kashaya*), reduced	—	—	256 parts
	3. Guda (jaggery)	*Saccharum officinarum*	—	200 parts
	4. *Dhataki*	*Woodfordia fruticosa* (L.) Kurz.	Flower	16 parts
	5. *Ajaji*	*Nigella sativa* L.	Fruit	1 part
	6. *Mustak*a (*musta*)	*Cyperus rotundus* Linn.	Rhizome	1 part
	7. *Sunthi* (ginger)	*Zingiber officinale* Roxb.	Rhizome	1 part
	8. *Darvi* (*daruharidra*)	*Berberis aristata* DC.	Stem	1 part
	9. Utpala	*Nymphaea stellata* Willd.	Flower	1 part
	10. *Haritaki*	*Terminalia chebula* Retz.	Whole plant	1 part
	11. *Bibhitaka*	*Terminalia bellirica* (Gaertn.) Roxb.	Whole plant	1 part
	12. *Amalaki*	*Phyllanthus emblica* L.	Whole plant	1 part
	13. *Amrasthi* (*Amra*)	*Mangifera indica* L.	Endosperm	1 part
	14. *Jiraka* (*sveta jiraka*)	*Cuminum cyminum* L.	Fruit	1 part
	15. *Vasa*	*Adhatoda vasica* Nees.	Root	1 part
	16. *Chandana* (*sveta candana*)	*Santalum album* Linn.	Heart wood	1 part

^a^Not applicable.

## Methods

### Study Setting

This study will be conducted at Vardhman Mahavir Medical College and Safdarjung Hospital, New Delhi, India.

### Eligibility Criteria

#### Inclusion Criteria

Participants will include those aged 20-50 years with menorrhagia—that is, regular (21-35 days) cycle with HMB loss, subjectively or objectively defined (Pictorial Blood Assessment Chart [PBAC] score of more than 100 points) [12], or prolonged bleeding (bleeding more than >7 days) for 3 consecutive cycles—who are willing and able to participate in the study.

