#### Exclusion Criteria

Participants with any of the following will be excluded: anemia (hemoglobin level <7%); hypertension; diabetes mellitus; hepatic or renal disease; cardiac disease; organic lesions of the reproductive tract due to conditions such as tuberculosis, carcinoma, and congenital deformities; pelvic inflammatory disease or cervicitis; evidence of malignancy, cervical intraepithelial neoplasia, or cervical carcinoma; history of untreated sexually transmitted disease or being HIV positive; past history of atrial fibrillation, acute coronary syndrome, myocardial infarction, stroke, or severe arrhythmia in the last 6 months; lactating women; current or previous use of oral contraceptive pills, glucocorticoids, antiandrogens, ovulation induction agents, antidiabetic drugs, antiobesity drugs, or other hormonal drugs recently (unless there is a washout period of 1 month); hypersensitivity to the trial drugs or any of their ingredients; currently participating in any other clinical trial or participated in past 6 months; or any other condition that the principal investigator thinks may jeopardize the study.

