### Outcome Measures

#### Primary Outcome Measures

Primary outcome measures are changes in the amount of uterine bleeding evaluated by the PBAC, changes in the duration of bleeding, and the attainment of a normal amount of blood loss during the interval of cycles, evaluated at baseline, the end of every cycle up to 3 cycles, and follow-up visits.

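### Entry does not require a raised baseline PBAC, yet attainment of normal blood loss is a primary outcome with no restriction to women who were abnormal at baseline

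*Protocol article*

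**What the plan says.** Under Inclusion Criteria, the protocol article asks for a regular cycle and then gives the bleeding condition that a woman must meet: "subjectively or objectively defined (Pictorial Blood Assessment Chart [PBAC] score of more than 100 points) [12], or prolonged bleeding (bleeding more than >7 days"). The routes are alternatives, and the PBAC threshold belongs only to the objective one. The Exclusion Criteria add no lower limit on PBAC.

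Primary Outcome Measures names three outcomes: PBAC change, duration change and, as the third, "the attainment of a normal amount of blood loss during the interval of cycles". None is limited to women abnormal at baseline, and no value is attached to normal.

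The Introduction describes normal menstruation as "with 3-5 days in durations and 50-60 mL of bleeding in normal color" and defines menorrhagia as a loss of 80 mL or more per cycle. Neither figure is converted to a PBAC score.

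The Sample Size section says "we anticipated a difference of 70 units in average PBAC score after treatment between the two groups", with an SD of 137 taken from a previous study.

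**The concern.** The entry rule and the attainment outcome do not fit together. A woman with a PBAC of 80 who finds her periods heavy is eligible. So is a woman who bleeds lightly for 9 days. If normal is PBAC of 100 or less, both have normal measured loss at entry, and if they stay there they are counted as having attained it, whichever treatment they receive.

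Two things follow. The attainment rate rises in both arms for a reason unrelated to treatment. The difference between arms shrinks, because these women add the same successes to each side. In a comparison with an active drug, two high and similar rates are easily read as similar efficacy.

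There is a milder effect on PBAC change. A woman entering at 80 would have to fall to 10 to show a 70-point drop, so she can contribute little to the 70-unit between-group difference on which the trial is sized.

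**Working it through.** **1. The plan's own figure.** Inputs from Sample Size: δ = 70, σ = 137, z-values 1.96 and 0.84.

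n per group = 2 × [137 × (1.96 + 0.84) / 70]² = 2 × 5.48² = 60.06

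The stated 60 per group reproduces. With 60 per arm, a two-sided t test at 0.05 has about 79% power for 70 units, so there is no reserve.

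**2. PBAC change if some women enter low.** Let f be the share entering with PBAC of 100 or less. The article does not give f; the values below are assumptions. SD is held at 137 with 60 per arm. Two cases are shown: these women show no between-arm difference, so the average effect is 70 × (1 − f); or they show a quarter of it (17.5 units), so the average effect is 70 × (1 − f) + 17.5 × f.

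| f | Effect, none in low entrants | Power | Effect, a quarter in low entrants | Power |
|---|---|---|---|---|
| 0% | 70 | 79% | 70 | 79% |
| 10% | 63 | 70% | 64.75 | 73% |
| 20% | 56 | 60% | 59.5 | 66% |
| 30% | 49 | 49% | 54.25 | 58% |

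**3. Attainment.** Take normal as PBAC of 100 or less, and suppose that women already normal stay normal. The article gives no attainment rates, so assume 60% vs 40% among women with raised PBAC, and f = 20%.

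- All women: 0.2 + 0.8 × 0.60 = 68% and 0.2 + 0.8 × 0.40 = 52%. The difference is 16 points instead of 20. Power with 60 per arm is about 44%.
- Only women raised at baseline: 60% vs 40%, with 0.8 × 60 = 48 per arm. Power is about 51%.

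In this illustration, restricting the denominator gains about 7 points of power although a fifth of the women are left out, because those women add no information on the difference.

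**4. Is baseline PBAC known before allocation?** The study schedule places PBAC at visit 1, the day of enrolment, and not at screening. Randomization and Allocation does not say when randomisation occurs relative to that assessment. In an open-label trial the order matters, because a restriction on baseline PBAC is safe only if allocation could not have influenced the score.

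**The case against.** A reader might infer that women who enter with low PBAC cannot improve on two of the three primary outcomes and have already met attainment at baseline. The documents do not support that. PBAC is a score, and 90 can still fall. Whether attainment is already met depends on a value that Primary Outcome Measures does not set; under a stricter mark, a woman at 80 to 100 need not be normal. A duration-only entrant has full room to improve on duration.

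Broad entry also has a stated reason: the Introduction says that a woman's own perception of her loss drives referral and treatment. That stands, and it is why narrowing entry to PBAC above 100 is not clearly right. Limiting the duration analysis to women bleeding more than 7 days is no better: it would drop women bleeding 6 or 7 days, who already exceed the 3 to 5 days that the Introduction calls normal.

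The power figures rest on an assumed share, an assumed effect in that share, and a fixed SD. The entry criteria of the study that supplied the SD are not visible. If its population was similarly mixed, the planning figures may already reflect some dilution, and subtracting it again would count it twice. No stated figure is wrong. Nor does randomisation leave a bias between arms: low entrants are expected equally in both, so the harm is dilution and inflated rates.

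What these arguments do not answer is the attainment outcome. A woman with no excess measured loss at entry can be counted as a success, and the article does nothing to prevent it. The definition of normal might be left to a fuller document, but the entry rule is stated here in full and conflicts with the outcome as stated.

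**Conclusion.** The point holds for attainment of normal loss, and in weaker form for PBAC change. Women may enter without a raised PBAC, and the attainment outcome is not limited to women who had excess loss to correct. On the only PBAC mark in the article, those entering at 100 or less can be counted as successes in either arm without change.

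The size cannot be determined, because the share of such women is not given. Under the assumptions shown, a 20% share would cut a 20-point attainment difference to 16, and power for PBAC change from about 79% to between 60% and 66%. These figures show direction and scale and are not estimates for this trial. The sample size calculation is arithmetically sound, and the entry criteria are a defensible choice. What needs correcting is the denominator of one primary outcome.

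**What to change.** Keep the entry criteria. Before analysis:

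1. Fix the PBAC value that counts as normal, for example 100 or less, to match the inclusion threshold.
2. Analyse attainment only in women above that value at baseline, by randomised arm, using a baseline PBAC recorded before allocation. Confirm that order from the site's records, since the article does not state it.
3. Keep all randomised women in the analyses of change in PBAC and change in duration, adjusted for the baseline value of the outcome.
4. Report results by entry route (subjective complaint, PBAC above 100, prolonged bleeding) as supportive.

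The rule applies equally to the 79 women enrolled by December 2024 and to later entrants. It uses data that the study schedule already collects and needs no change to recruitment. The cost is a smaller denominator for attainment, which in the illustration above is more than repaid by the undiluted difference.
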